### Data analysis

Data collected in this research will be stored and processed in computerized database using the Microsoft Office Excel 2010 and Statistical Package for the Social Sciences (SPSS) version 20.0 software. Descriptive and inferential statistics of collected variables will be performed, and data will be presented through tables, charts and figures.

Statistical analysis of comparison and correlation of data obtained will be performed. The Kolmogorov-Smirnov test will be performed to analyze sample normality. Likewise, Pearson or Spearman tests will be used for correlational analyses. Categorical variables will be analyzed using the chi-square test or Fisher’s exact test. To compare the KAI and STAI assessment with the intervention and control groups, Student’s t-test will be applied. Comparing the IAC and IDATE classification with the group of intervention and control, the chi-square test (χ²) will be applied. Being adopted throughout the study a significance level of 5% at which p = 0.05.

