### Sample size

The sample is probabilistic and simple random. Sample size calculation was performed using the G Power software, version 3.1.9.2 (available at: http://www.gpower.hhu.de/). The calculation was performed considering the study by Bernardi et al. [20] that evaluated the IDATE score in caregivers of children and adolescents with cancer. Thus, considering the Cohen effect size of 0.80, test power of 0.80 and significance level of 5% (p-value < 0.05), the study had 26 participants in the Control Group (CG) and 26 participants in the Experimental Group (EG), totaling a sample of 52 study participants.

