### Allocation

The randomization of participants will be carried out through the www.randomizer.org website, which will previously select participants for each group (CG and EG) by simple randomness and without the influence of researchers. The site generates a list with the sequence of participants equally divided into the two intervention groups. It is noteworthy that the allocation of participants will be carried out by a researcher who is not involved in the intervention. Additionally, the allocation will be hidden.

It is noteworthy that randomization will avoid participant selection bias and will allow groups to be compared in terms of their known and unknown risk factors.

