### Intervention

The intervention that will be used in EG is the application of a multimedia strategy associated with the Institution’s standard guidelines. The multimedia strategy is the exhibition of a digital animation film with duration of 12 minutes and 22 seconds addressing the pediatric chemotherapy treatment process.

The film is an educational technology developed by Pinheiro et al. [21], during the master’s degree of the main author, using as reference a manual of a service of Hematology and Oncology of the University Hospital of Santa Maria (HUSM), specialized in the treatment of childhood cancer in partnership with students and professors of the Design, Digital Games and Journalism courses at the Franciscan University (UFN). It was validated by experts in the field and by the target audience and authorized to carry out the study, but it is not available for free access.

The digitally animated film will be shown in a quiet room, before starting chemotherapy. The caregiver will be provided with a headset and a tablet to watch the movie.

The digital animation film used in the study generally addresses the concept of chemotherapy, chemotherapy administration routes, most frequent side effects and general care during treatment. The film emphasizes health education about chemotherapy for the caregiver.

GC will receive instructions verbally. The standard verbal instructions are provided as supplementary material.

The intervention period will be carried out in two days consisting of three stages: the first stage is performed on the first day of contact after admission of the child/adolescent to the chemotherapy unit with the caregiver who, after accepting and signing the informed consent form, will be included in the search.

The second stage is performed on the second day of contact, which will be on the child’s first day of chemotherapy, and before starting the procedure, the main researcher will apply the instrument to assess the level of anxiety (State Trait Anxiety Inventory—STAI) of caregivers in both groups (CG and EG).

Subsequently, the intervention will be carried out according to the groups formed, in which the principal investigator will carry out health education using the multimedia strategy associated with the standard guidelines in the EG and standard guidelines in the CG.

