### Primary outcomes

The primary outcome includes reduction in the level of anxiety of caregivers of children and adolescents undergoing chemotherapy. The before and after STAI anxiety data will provide the levels of anxiety of CG and EG to evaluate which intervention had the best effect.

Furthermore, data obtained on participants’ level of anxiety can be used to compare levels before and after intervention of each participant, whether in CG or EG; levels of anxiety between groups before and after intervention, assessing the management of anxiety according to the intervention performed.

STAI response possibilities range from 1 to 4, where: 1 = almost never; 2 = sometimes; 3 = often; and 4 = almost always. The final STAI score is directed to the level of anxiety classified as 20 to 40 points–low level; 41 to 60 points–moderate level; 61 to 80 points–high level.

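### STAI is compared between groups with an unadjusted t-test that is valid but wastes the baseline measurement, and the protocol does not say whether post-intervention or change scores are tested

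*Protocol article*

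**What the plan says.** Under Primary outcomes the article makes reduction of caregiver anxiety the primary outcome and adds: "The before and after STAI anxiety data will provide the levels of anxiety of CG and EG". Under Intervention, on the day chemotherapy starts and before the intervention, "the main researcher will apply the instrument to assess the level of anxiety (State Trait Anxiety Inventory—STAI) of caregivers in both groups". A second researcher, who does not know the allocation, repeats the STAI 30 minutes after the intervention on the same day (assessment F1).

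The Data analysis section gives the between-group test: "To compare the KAI and STAI assessment with the intervention and control groups, Student’s t-test will be applied". A chi-square test is added for the low, moderate and high classes. The article mentions no covariate, regression or repeated-measures model. It does not say whether the t-test is applied to the F1 score or to the change from the pre-intervention score. The Data collection instrument section says the STAI measures both trait and state anxiety, and the article does not say which of the two the primary test uses.

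The Sample size section assumes a Cohen effect size of 0.80, power of 0.80 and a 5% significance level, giving 26 per arm, "totaling a sample of 52 study participants". Under Allocation, "The site generates a list with the sequence of participants equally divided into the two intervention groups"; no stratification on baseline anxiety is described.

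**The concern.** A pre-intervention score on the outcome scale is collected from every caregiver in both arms, but the named test does not condition on it. On F1 scores, the t-test ignores the baseline. On change scores, it subtracts the whole baseline when only a fraction r of a baseline difference is expected to carry over, so it over-corrects. For r below 0.5 it is also less efficient than the F1-only test. ANCOVA (F1 score on group plus baseline score) estimates that fraction from the data and, apart from one degree of freedom, is at least as efficient as either.

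The t-test is named in the protocol, so this concerns a stated choice and not a detail left to an unseen analysis plan. At stake is the precision of the primary comparison in a trial with little power to spare. A further cost is that two different t-tests fit the same sentence, and they can give different answers on the same data.

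**Working it through.** **Inputs.** From the Sample size section: n = 26 per arm, d = 0.80, power 0.80, α = 5%. Sidedness is not stated; two-sided is assumed because it reproduces the plan's figure. Further assumptions, none given in the documents: r = 0.3, 0.5 and 0.7, and equal SDs before and after the intervention.

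**The plan's own figure.** For a two-sided two-sample t-test, the noncentrality is d·√(n/2) = 0.80 × √13 = 2.88 on 50 degrees of freedom. The noncentral t gives power 0.807 at 26 per arm, and 26 is the smallest n that reaches 0.80. A one-sided test would need 21. The sample size therefore matches an unadjusted two-sided t-test.

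**Reading A: d is in units of the single-time-point SD.** The effect in units of each method's own residual SD is:
- post-score t-test: d, that is 0.80 at every r;
- change-score t-test: d/√(2(1 − r)), that is 0.676, 0.800 and 1.033;
- ANCOVA: d/√(1 − r²), that is 0.839, 0.924 and 1.120, on 49 degrees of freedom.

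| Power, 26 per arm | r = 0.3 | r = 0.5 | r = 0.7 |
|---|---|---|---|
| Post-score t-test | 0.807 | 0.807 | 0.807 |
| Change-score t-test | 0.667 | 0.807 | 0.955 |
| ANCOVA | 0.842 | 0.904 | 0.977 |

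The effect detectable with 80% power is 0.79 SD for the post-score t-test, against 0.76, 0.69 and 0.57 SD for ANCOVA. If the true effect were 0.5 SD, power would be 0.424 for the post-score t-test, against 0.457, 0.532 and 0.697 for ANCOVA.

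**Reading B: d is in units of the SD of change.** The change-score t-test then has power 0.807 at every r. The ANCOVA effect is 0.80 × √(2/(1 + r)), that is 0.992, 0.924 and 0.868, with power 0.939, 0.904 and 0.866. Here the gain over the change-score test shrinks as r rises.

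**No correlation at all.** At r = 0 under reading A, ANCOVA has power 0.807, the same as the post-score t-test to three decimals.

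**Chance baseline differences.** The standard error of the baseline difference is √(2/26) = 0.277 SD. The chance of a gap above 0.3 SD in either direction is about 28%, and above 0.5 SD about 7%. A gap of one standard error moves a post-score comparison by r × 0.277, that is 0.14 SD at r = 0.5 and 0.19 SD at r = 0.7. It moves a change-score comparison the other way by (1 − r) × 0.277, that is 0.14 and 0.08 SD.

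**The case against.** The strongest reply is that nothing here is an error. The t-test holds its 5% type I error under randomisation, and the planned size is right for it. That stands. A reader might infer that the test is invalid or the sample size miscalculated; the reproduction of 26 per arm shows otherwise.

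A reader might also infer that chance baseline imbalance is left uncorrected. That holds only if F1 scores are tested. Because the outcome is worded as a reduction judged on before and after data, a change-score test is at least as natural a reading, and it does use the baseline, though too much of it. Nor do the 28% and 7% chances of imbalance show bias: over repeated randomisations they are already part of the t-test's standard error, and they represent precision that adjustment would recover.

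The size of the loss also depends on which t-test is meant. Under reading A it is small for a post-score test at low r (0.807 against 0.842 at r = 0.3) and for a change-score test at high r (0.955 against 0.977 at r = 0.7). It is large only for the opposite pairings. A high r cannot be taken for granted: same-day repetition of one instrument makes a positive r plausible, but the two assessments are made by different interviewers, which may lower it. The article also does not say which SD d refers to. All of this stands and limits how much gain can be claimed.

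It does not remove the point. ANCOVA has higher power than either t-test at every r tabulated under reading A and than the change-score test under reading B, and it costs nothing material even at r = 0.

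**Conclusion.** The point holds as one of precision and specification. The protocol fixes a valid but less efficient test for its primary outcome and leaves open which score is tested. Under reading A, ANCOVA raises power from 0.81 to between 0.84 and 0.98 against a post-score t-test, and from between 0.67 and 0.95 to the same range against a change-score t-test. Under reading B, it raises power from 0.81 to between 0.87 and 0.94 against a change-score t-test. These figures rest on an assumed r of 0.3 to 0.7, equal SDs before and after, and a two-sided 5% test. The documents do not support a claim that the trial is underpowered for its stated effect or that its result would be biased. The change should be made, but the trial's validity does not depend on it.

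**What to change.** In the Data analysis section, replace the t-test as the primary analysis of STAI with wording such as: *The primary analysis is a linear model of the post-intervention (F1) state-anxiety STAI score on group, adjusted for the pre-intervention state-anxiety STAI score, reporting the adjusted mean difference with its 95% confidence interval and two-sided p-value.* Keep the t-test as supportive, and say whether it uses F1 or change scores. Naming state anxiety also settles which STAI score is primary; the article itself describes state anxiety as the transient part and trait anxiety as the usual level.

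The sample size can stay at 52. State in the Sample size section which SD the effect size of 0.80 refers to.

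The cost is a sentence or two of text and one degree of freedom, with no extra data or participants. The SPSS version named in the protocol fits this model. The Study status section describes the trial as still preparing to recruit, so on that footing the change can be prespecified.

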## Introduction

Childhood cancer (from 0 to 19 years of age) represents a public health problem, affecting approximately 300,000 new children worldwide each year, with greater increase in developing countries. Furthermore, the World Health Organization (2022) estimates a prevalence of childhood cancer of approximately 600,000 cases worldwide, with leukemia, central nervous system tumors and non-Hodgkin’s lymphoma being pointed out as the most frequent [1].

It is noteworthy that childhood cancer presents a different behavior if compared to cancer in adults, being marked by uncertain mutations and non-evidenced risk factors, making it a challenge for the scientific community mainly related to early diagnosis and treatment [2, 3].

In this context, in relation to treatment, chemotherapy is the basis for therapy, and can be performed alone or associated with surgery and radiotherapy, considerably contributing to improve the prognosis and survival of patients [4].

However, chemotherapy treatment causes the development of negative feelings such as fear and anxiety among parents or caregivers, mainly related to the stigma of the disease, such as not knowing the therapy, its effects and the purpose of treatment [5].

Furthermore, it is in the impact of the diagnosis and definition of treatment that these feelings emerge, consisting a difficult period for the assimilation of information verbally transmitted by health professionals to caregivers. When information is transmitted in an accumulated way and with the use of technical language, caregivers /parents experience greater tension and lack of understanding about the disease and treatment [6, 7].

It is necessary to take into account that the caregiver may not have sufficient schooling to understand technical terms, and it is necessary to facilitate communication using language accessible to all, which should be enlightening, simple and objective [8].

Thus, the guidelines provided to caregivers / parents of children / adolescents undergoing chemotherapy are part of the activities of health professionals and among them the nurse, who plays an essential role in the health education process. Basic care with food, hygiene, hydration and management of chemotherapy side effects constitute important standard guidelines for caregivers and are provided by health professionals [9, 10].

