### Data collection instrument

Two instruments will be used for data collection:

State Trait Anxiety Inventory (STAI) [22], an instrument that assesses trait and state anxiety, the first relates to the caregiver’s usual anxiety and the second concerns transient anxiety related to some stressful event. Thus, the aim was to obtain the level of anxiety of participants before and after intervention, comparing these values to evaluate the management of anxiety by intervention, as well as comparing values between groups, evaluating the best management.Knowledge Assessment Instrument (KAI), adapted from the study by Oliveira, Souza and Pellanda [23], which has the aim of assessing the effectiveness of the multimedia strategy used in the acquisition of knowledge by participants.

This instrument has a semi-structured questionnaire composed of three stages: the first consists of sociodemographic data of participants; the second contains information about previous guidelines by other professionals and the participant’s opinion about the intervention performed in order to report whether the intervention was able to resolve doubts about the chemotherapy procedure. The third stage consists of nine questions about the chemotherapy process, to quantify the knowledge that participants obtained on the subject after intervention. The STAI and KAI are validated and reliable instruments used in studies with adults and caregivers [22, 23].

The KAI and STAI instruments will be applied as an interview, clarifying the instrument’s questions and marking the alternative chosen by the research participant. It should be noted that STAI was translated and validated into Portuguese by Biaggio, Natalício and Spielberge [22].

The Knowledge Assessment Instrument (IAC) is a form prepared by the main researcher based on the questionnaire used in the study by Oliveira, Souza and Pellanda (2016) in portuguese.

Fig 1 shows the detailed steps of the study, with SPIRIT schedule of enrollment, interventions and assessments:

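### The unadjusted t-test on KAI is valid but may be less precise than a model with schooling; prior guidance, asked only after the intervention, cannot serve as a baseline variable

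*Protocol article*

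**What the plan says.** The Data analysis section of the protocol article fixes the method. For the step "To compare the KAI and STAI assessment with the intervention and control groups", it names Student's t-test. No covariate is named for this comparison.

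Under Data collection instrument, the KAI is a form in three parts. Of the first two parts the article says: "the first consists of sociodemographic data of participants; the second contains information about previous guidelines by other professionals". The second part also asks for the caregiver's opinion of the intervention. The third part is the nine knowledge questions, which Secondary outcomes scores from 0 to 9.

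The Intervention section gives only the STAI before the intervention. The KAI is given once, 30 minutes after the intervention ends (F1). The text shown describes no earlier collection of the sociodemographic or prior-guidance items. Fig 1 is not available to check.

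The Introduction remarks that "the caregiver may not have sufficient schooling to understand technical terms". Allocation is described as simple randomisation into two equal groups, with no stratification.

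**The concern.** Two separate matters arise.

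**Precision.** The STAI has a pre-intervention value that could be used to adjust its comparison. KAI has none, so any gain in precision must come from another baseline characteristic. Schooling is a natural candidate for a knowledge score, and the Introduction gives a reason to expect it to affect understanding. With 26 per arm and no stratification, the arms may differ in schooling by chance, and the t-test does not allow for this.

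**Timing.** The background questions sit inside a form that is first given after the intervention. Whether other professionals had already given guidance is then a matter of recall, asked beside the caregiver's opinion of the session just received. The experimental arm has also seen a film of 12 minutes 22 seconds. The answer can therefore depend on arm. Adjusting for it as now collected could bias the comparison. Caregivers who leave before F1 would also have no background record from this form.

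**Working it through.** **Inputs from the protocol article (Sample size).** The calculation rests on "considering the Cohen effect size of 0.80, test power of 0.80 and significance level of 5% (p-value < 0.05", and gives "26 participants in the Control Group (CG) and 26 participants in the Experimental Group (EG), totaling a sample of 52 study participants". Sidedness is not stated. The effect size comes from a study of the anxiety score; no effect size is given for KAI.

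**Inputs assumed.** The correlation r between schooling and KAI is not in the article, so a range from 0 to 0.5 is shown. That schooling is one of the sociodemographic items is also assumed. The calculation treats KAI as roughly normal.

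**Step 1: reproduce the plan's figure.** For a two-sided t-test at 5%, the noncentrality is d × √(n/2) = 0.80 × √13 = 2.884, with 50 df and critical value 2.009. Power is 0.807 at 26 per arm and 0.791 at 25. So 26 per arm is the smallest size that reaches 0.80, and the stated 52 reproduces.

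**Step 2: validity of the t-test.** In 20,000 simulated trials per setting, with covariates that the test ignores, its type I error was 0.051 when they explained none of the outcome variance and 0.048 when they explained 20%. Leaving covariates out does not make the test wrong.

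**Step 3: add schooling as one covariate.** The residual variance is multiplied by (1 − r²), the error df fall from 50 to 49, and the expected cost of chance imbalance in one covariate multiplies the variance by 1 + 1/(52 − 1 − 3) = 1 + 1/48. So:

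noncentrality = d × √13 / √[(1 − r²)(1 + 1/48)]

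Example, d = 0.80 and r = 0.3: 2.884 / √(0.91 × 1.0208) = 2.993. With critical value 2.010, power is 0.835.

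| Assumed r | Power, d = 0.80 | Power, d = 0.50 | SE relative to unadjusted |
|---|---|---|---|
| t-test, no covariate | 0.807 | 0.424 | 1 |
| 0 | 0.799 | 0.417 | 1.010 |
| 0.1 | 0.803 | 0.420 | 1.005 |
| 0.2 | 0.815 | 0.431 | 0.990 |
| 0.3 | 0.835 | 0.450 | 0.964 |
| 0.4 | 0.863 | 0.480 | 0.926 |
| 0.5 | 0.898 | 0.524 | 0.875 |

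The d = 0.50 column is illustrative; that value is not in the article.

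**Step 4: break-even.** Adjusted and unadjusted power at d = 0.80 are equal when schooling explains about 2% of KAI variance, that is r of about √0.021 = 0.15. The worst case in the table is 0.807 − 0.799 = 0.008. More terms raise the threshold, to about 4% for two and 6% for three.

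**Step 5: timing, item by item.**
- Schooling is a fixed fact. A film shown half an hour before cannot change it, so asking late does not bar adjusting for it.
- Recalled prior guidance is not fixed in this sense. It is reported after the trial's own guidance and can differ by arm for that reason.
- A caregiver who leaves before F1 lacks the background items and the KAI score alike. A Day 1 covariate would not bring that caregiver into the KAI model, but would allow a description of who left.

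**The case against.** The strongest reply is that nothing here is wrong. A t-test is valid in a randomised comparison, KAI is secondary, the sample size rests on the anxiety score, and covariate adjustment is often left to an analysis plan that is not shown. This stands as far as validity goes. What remains is that the article does not leave the KAI method open: it names an unadjusted test, and it places the background questions after the intervention. No later analysis plan can undo that timing.

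Four stronger readings are tempting, and the article does not support them.

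- *Precision is lost.* This depends on a correlation the article does not give. Below about 0.15 the adjusted analysis is marginally worse, and at 0.2 the gain is under one point.
- *The protocol names schooling as a driver of the knowledge score, collects it and never uses it.* The Introduction makes a background remark in favour of plain language. Schooling is not listed among the collected items. Data analysis also plans descriptive and correlational work on the collected variables, so only the between-arm comparison can be said to omit it.
- *Late collection spoils all the background data.* It affects recalled prior guidance, not schooling. The article does not propose prior guidance as a covariate, so no planned analysis is contaminated.
- *Missing background data weaken the KAI comparison.* Those who leave before F1 lack the outcome too.

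**Conclusion.** The point holds as a minor one about efficiency and data collection. The KAI t-test is valid. Adding schooling costs less than one point of power at worst. At d = 0.80 it gains about 3 to 9 points if the correlation with KAI lies between 0.3 and 0.5 (0.835 − 0.807 = 0.028; 0.898 − 0.807 = 0.091).

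These figures rest on three assumptions: that schooling is among the sociodemographic items, that the correlation lies in the range shown, and that an effect size stated for anxiety is a fair illustration for KAI.

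The timing point does not depend on the first. As now collected, prior guidance should not be used as a baseline variable. Day 1 collection would also allow caregivers who leave before F1 to be described.

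**What to change.** 1. In Data analysis, state that KAI at F1 is compared between arms by a linear model with arm and schooling, schooling entered as one prespecified term (for example, years). Keep Student's t-test as a supporting analysis. State that schooling is collected.
2. In Data collection instrument and Intervention, move the sociodemographic and previous-guidelines questions to Day 1 after consent. Leave the opinion items and the nine knowledge questions at F1.
3. If the previous-guidelines item stays at F1, say that it will be reported descriptively and not used as a baseline covariate.

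The cost is one degree of freedom and a change in when existing questions are asked. Items 1 and 2 can be adopted independently. By its Study status section, the trial was still preparing to recruit, so the move would need no change to data already collected.
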